### Sample size

The sample size has been calculated with NCSS-PASS software. At 5 years, peri-implant bone loss in metal-resin/metal-ceramic IFCDPs was 0.9 ± 0.4 mm and peri-implant bone loss in ceramic IFCDPs was 0.6 ± 0.1 mm [26]. In the proposed study, the criterion for significance is set at *α* = 0.05 (type I error) and *β* = 0.10 (type II error). The analysis is two-tailed. Assuming a dropout rate of 20%, in order to determine if there is a difference in the degree of bone loss between the two groups, 22 cases per group and 44 cases in total will be required. A previous study included 20 edentulous subjects who received two mandibular implants [10]. The abutments were either titanium or zirconium dioxide (non-submerged implant placement, within-subject comparison, left-right randomization). After 3 months, mean absolute counts of *Porphyromonas gingivalis* of the titanium vs. zirconia abutment were 1,000,000 ± 0 vs. 64,000 ± 36,770, respectively. However, the difference between groups was not evaluated in this study. Mean absolute counts (mean) for *Prevotella intermedia* of the titanium vs. zirconia abutment were 600,088 ± 952,117 vs. 3,600,089 ± 804,935, although the difference between the two groups was not evaluated. In this study, the criterion for significance will be set at *α* = 0.05 (type I error) and *β* = 0.10 (type II error). The analysis will be two-tailed. Assuming a dropout rate at 20%, in order to determine if there is a difference in the amounts of *P*. *gingivalis* and *P. intermedia* between the two groups, three patients per group and six patients in total will be required.

In summary, the total sample size will be 44 (22 per group).

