#### Clinical monitoring and X-ray assessment

Continuous variables will be described as the mean ± standard deviation or median. Grade and qualitative data will be described as a percentage. Age and other basic information between groups will be compared with the independent *t* test. Gender, implant survival rates, peri-implantitis rates, and peri-implant mucositis rates between the test and control groups will be compared using the chi-square test. PD and X-ray indices between groups will be compared using the independent *t* test. The differences in PLI and BI between the two groups will be evaluated, as well as the differences in PLI and BI over a period of 10 follow-ups. A generalized estimating equation will be used to eliminate possible internal correlations between multiple implants of the same patient. A Cox regression model will be used to exclude the influences of the shapes of the intaglio surface, the distances between the inserted implants, and other cofounders affecting the primary and secondary outcome variables. A probability (*p*) value of < 0.05 will be considered statistically significant.

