### Withdrawal and missing data processing

The patients will be informed at the beginning of the study of the right to withdraw at any time without providing a reason. Even in the event of a withdrawal, the patient will still receive treatment.

If a participant has taken an antibiotic in the last 3 months before a follow-up visit, submucosa samples will be collected, the results of clinical examinations (surface roughness) will be recorded, and X-ray examinations will be conducted. The data obtained from this follow-up will be discarded. However, we still include this participant in the following visits and do the regular periodontal maintenance. If there was no antibiotic use within 3 months prior to the next follow-ups, the data will be recorded.

Any patients who reported smoking during the follow-up period will be excluded from the study.

The possibility of loss to follow-up was considered and calculated as a part of the sample size estimation.

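### The 5-year bone-loss t test, read as written, leaves dropouts' earlier annual films unused; a repeated-measures model would use them at little cost

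*Protocol article*

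**What the plan says.** - **Planning basis (Protocol article, Sample size).** The 5-year planning value for the titanium arm is that "peri-implant bone loss in metal-resin/metal-ceramic IFCDPs was 0.9 ± 0.4 mm". For the zirconia arm the corresponding value is that "peri-implant bone loss in ceramic IFCDPs was 0.6 ± 0.1 mm". The calculation is two-sided at 5% with 90% power. Its dropout allowance is worded as follows: "Assuming a dropout rate of 20%, in order to determine if there is a difference in the degree of bone loss between the two groups". The result given is 22 per group (44 in total).
- **Films (Table 1; X-ray assessment).** Films are scheduled at Months 0, 12, 24, 36, 48 and 60.
- **Test (Statistical analysis, Clinical monitoring and X-ray assessment).** The sentence that begins "PD and X-ray indices between groups will be compared using the independent" names the two-sample *t* test. The comparison across follow-ups in that section names only the plaque and bleeding indices. The stated purpose of the generalized estimating equation (GEE) is correlation among several implants in one patient.
- **Loss to follow-up (Withdrawal and missing data processing).** "The possibility of loss to follow-up was considered and calculated as a part of the sample size estimation". The same section drops data from visits that follow recent antibiotic use and removes patients who report smoking. Both rules can leave further patients without a usable Month 60 value.

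**The concern.** Enrolling more patients restores precision. It does nothing about which patients are left to compare. A *t* test at Month 60 on those who still have a film estimates the randomised difference without bias only if leaving is unrelated to bone loss, or if it shifts both arm means equally. The planning figures make an equal shift unlikely when leaving is related to bone loss. With SDs of 0.4 and 0.1 mm, the same selective mechanism moves the titanium mean much further than the zirconia mean.

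The data that would reduce the problem are already being collected. A patient lost after the Month 36 film has three follow-up values that say a good deal about the likely 5-year value. A single-visit *t* test uses none of them.

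**Working it through.** **1. The plan's own figure.** Inputs from Sample size: difference 0.9 − 0.6 = 0.30 mm; SDs 0.4 and 0.1; two-sided α 0.05; power 0.90; dropout 20%.

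- Pooled SD = √[(0.4² + 0.1²)/2] = 0.2915 mm.
- n per group = 2 × [0.2915 × (1.960 + 1.282)/0.30]² = 19.85, so 20 by the normal formula. The equal-variance *t* gives 21 and the Welch *t* gives 22.
- Divided by 0.8 for dropout: 25, 27 or 28 per group.

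The stated 22 equals the Welch figure before any dropout allowance and is not reproduced with one. This is a separate matter, but it means that the allowance relied on in the missing-data section does not appear to be in the 44.

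**2. Dropout unrelated to bone loss.** The number off study is 0.20 × 44 = 8.8, about 9. Completers per arm are 22 × 0.8 = 17.6, about 18. At 18 per arm, power is 0.83 (Welch) to 0.87 (normal), and the difference stays at 0.30 mm. In simulation, completers-only power was about 84-85% against 88-89% using all annual films, a gain of about 4 points.

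**3. Why unequal SDs matter.** Suppose selection lowers each arm's completer mean by the same number k of that arm's SDs. Then:

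completer difference = (0.9 − 0.4k) − (0.6 − 0.1k) = 0.30 − 0.30k.

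The extreme case is that the 20% with most loss in each arm all leave. Then k = φ(z₀.₈)/0.8 = 0.35, the means are 0.76 and 0.565 mm, and the difference is 0.195 mm. That is an outer limit for equal 20% dropout, not a forecast.

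**4. Graded selection (illustrative simulation).** None of the following assumptions is in the documents: linear accrual of bone loss, adjacent-year correlation 0.8-0.9, 20% dropout overall, and odds of leaving after each film that multiply by about 2.0 or 3.3 per SD of bone loss already seen (logistic slopes 0.7 and 1.2). The result depends on which SD is meant.

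| Dropout depends on | Dropout, titanium / zirconia | Completer difference | Using all films |
|---|---|---|---|
| Nothing | 20% / 20% | 0.30 mm | 0.30 mm |
| Loss relative to own arm's SD | 20% / 20% | about 0.25-0.28 mm | about 0.30 mm |
| Absolute loss (common SD), slope 0.7 | about 28% / 12% | about 0.22-0.24 mm | about 0.30 mm |
| Absolute loss (common SD), slope 1.2 | about 33% / 7% | about 0.17-0.20 mm | about 0.30 mm |
| Low-loss patients leave (slope −0.7) | about 20% overall | about 0.33-0.34 mm | about 0.30 mm |

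In the second row, Welch power at 22 randomised per arm is about 72-77%. The last column is a maximum-likelihood estimate under dropout that depends only on films already observed.

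**The case against.** **This is a condensed article, and dropout handling belongs in the SAP.** That would dispose of the point if the article were silent. It is not: it has a missing-data section that gives an answer, and it names the test. A separate plan could still add a method.

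**A reader might infer that the protocol discards earlier films by rule.** It does not say so. No visit, completers set or exclusion of earlier films is stated for the *t* test, and the Month 12 and 36 films may be used in the 1- and 3-year interim analyses. The Month 60 completers-only analysis is the natural reading, not a quoted rule. The GEE does not clearly rescue it: its stated purpose is implants within a patient, and an unweighted GEE would still need dropout unrelated to outcome.

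**A reader might infer that 20% of patients are expected to leave, or that the test is biased as it stands.** The 20% is a planning allowance. Nothing in the protocol links leaving to bone loss. The planned losses of 0.6-0.9 mm are well below its own threshold of more than 2 mm for peri-implantitis, so it is not shown that patients would leave because of them. The direction is also open, as the last row of the table shows. All of this stands.

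**The large effects depend on a modelling choice.** This also stands. Differences well below 0.25 mm in the graded simulations arise only when dropout follows absolute bone loss, which makes dropout unequal between arms. The gain from the mixed model is also somewhat flattered when power is taken from empirical standard errors: a *t* reference with 17 degrees of freedom lowers that model's power by about 4 to 5 points.

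**Conclusion.** The point holds as a cheap improvement. The protocol fixes a single-visit test for the outcome that drives its sample size and treats loss to follow-up only as a matter of numbers, while collecting annual films that could do more.

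If dropout is unrelated to bone loss, the cost is a few points of power and no bias. If patients with more bone loss leave, the 0.30 mm difference shrinks, illustratively to about 0.25-0.28 mm (power about 72-77%) with equal dropout in both arms, and to about 0.17-0.24 mm if dropout falls mainly on the titanium arm. If patients with less bone loss leave, the difference is overstated.

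These figures rest on the planning means and SDs and on assumed accrual, correlation and dropout strength, so they illustrate and do not predict. The documents do not support the claim that the planned comparison will be biased. They support the narrower claim that it is open to bias in a way that the earlier films could reduce.

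**What to change.** Replace the *t* test as the 5-year bone-loss analysis with the Month 60 contrast from a repeated-measures mixed model. The response is patient-mean bone loss at Months 12, 24, 36, 48 and 60. Include arm, visit, arm-by-visit and the Month 0 bone level, let the variance differ by arm, and use small-sample degrees of freedom. Every randomised patient with at least one usable follow-up film then contributes, including those whose Month 60 value is missing. Averaging over implants within a patient also deals with clustering for this outcome.

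Add one sensitivity analysis that assumes worse bone loss after dropout than the model predicts, and report dropout by arm and year beside it.

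The cost is analysis wording and a little more work, possibly outside SPSS if arm-specific covariance is not convenient there. It needs no new visits, films or patients. The model relies on dropout being explained by the films already observed. That cannot be verified, but it is a weaker assumption than the completers-only test makes, and the sensitivity analysis probes it.

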## Discussion

The aim of the current study is the effect of the properties of the prosthetic material on peri-implant microbiota diversity and abundance. The authors hypothesize that the corrosion and aging of framework may have a crucial role in the selection of bacteria that adhere to the pellicles on the prosthesis surface. Considering that biofilm formation and the microbiota might further influence the long-term condition of the peri-implant mucosa and bone loss, our data will widen current views of the etiology of peri-implant diseases, promote updated treatment strategies, and prevent peri-implant diseases.

Specifically, by controlling surface roughness and analyzing submucosal microbiota, our research targeted at edentulous patients with full-arch implants will provide scientific evidence of the differences in the material properties of zirconia and titanium in terms of the influence on biofilm formation. A previous study indicated that a roughness average of 0.2 μm was the threshold for maximum reduction of bacterial adhesion on abutment surfaces [36, 37], while the national standard of 0.025 μm was adopted for all prostheses in this study. A previous in vivo study found that there was no universal optimum roughness that can prevent adhesion of all bacterial species [38], and surface charge, surface energy, surface topography, and material stiffness all influence the bacterial response. Thus, a clinical index was used to determine which material is more susceptible to biofilm formation. To compare the pathogenicity of plaque between the two groups, analysis of oral flora is crucial. As a possible limitation, although the surfaces of the two frameworks were polished to the same roughness at the time of restoration, changes to the surface roughness of the two materials due to long-term use could not be prevented. On the one hand, the oral cavity is an aggressive environment. Material surfaces in the mouth are covered by the salivary pellicle (up to 1000 nm thick [39]), which can also alter the nanotopography of restorative materials [40], thereby greatly influencing surface roughness. Mechanical stimulus, temperature, and pH conditions can also favor additional bacterial adhesion to the prostheses and alter material surface characteristics. On the other hand, during the implementation of this trial, regular periodontal maintenance (ultrasonic devices with polyetheretherketone-coated tips) combined with erythritol air-polishing will be conducted. The procedure will be performed by experienced dental hygienists in order to limit the effect of periodontal maintenance on the surface properties of dental zirconia ceramics and the effect of titanium or zirconia implant abutments on epithelial attachments after periodontal maintenance. Furthermore, the mechanical properties of zirconia frameworks with ceramic veneering differ from those of titanium frameworks veneered with acrylic resin. Previous studies have revealed that technical complications occasionally occur, although at low incidences [41, 42]. The incidences of wear and fracture are 19.4% and 0.7%, respectively, for titanium frameworks and 7.3% and 5.9% for zirconia [43]. In consideration of possible changes in roughness due to chipping, further analysis, including the incidence of chipping, is needed.

The results of this trial will support a tangible decision-making process for choosing appropriate dental implant-based prostheses for edentulous patients.

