**Methods:**

The proposed study is designed as a 5-year randomized controlled trial. We plan to enroll 44 edentulous (mandible) patients seeking full-arch, fixed, implant-supported prostheses. The participants will be randomly allocated to one of two groups: group 1, in which the participants will receive zirconia frameworks with ceramic veneering, or group 2, in which the participants will receive titanium frameworks with acrylic resin veneering. Ten follow-up examinations will be completed by the end of this 5-year trial. Mucosal conditions around the implants will be recorded every 6 months after restoration. Peri-implant submucosal plaque will be collected at each reexamination, and bacteria flora analysis will be performed with 16S rRNA gene sequencing technology in order to compare differences in microbial diversity between groups. One week before each visit, periodontal maintenance will be arranged. Each participant will receive an X-ray examination every 12 months as a key index to evaluate the marginal bone level around the implants.

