**Discussion:**

The current study aims to explore the oral microbiology of patients following dental restoration with zirconia ceramic frameworks or titanium frameworks. The features of the microbiota and the mucosal condition around the two different materials will be evaluated and compared to determine whether zirconia is an appropriate material for fixed implant-supported prostheses for edentulous patients.

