## Objectives

The aims of the study are (1) to investigate and compare the implant survival and biological complication rates between two different restorative materials on full-arch fixed implant-supported rehabilitation and (2) to compare the effect of two different restorative materials on the diversity of microbiota colonizing full-arch fixed implant-supported restorations (i.e., zirconia frameworks with ceramic veneering vs. titanium frameworks with acrylic resin veneering).

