## Methods and study design

### Study design and setting

The proposed study is designed as a pragmatic randomized controlled trial with a 5-year follow-up period. A Consolidated Standards of Reporting Trials diagram is presented in Fig. 1. We plan to enroll 44 edentulous patients (mandible) in need of dental implant-based prostheses. The goal of the treatment protocol is to rehabilitate these patients with full-arch fixed implant-supported prostheses with placement of 4–6 titanium implants in the mandible. The patients will be randomly assigned to receive restorative materials of zirconia frameworks with ceramic veneering (Fig. 2) or titanium frameworks with acrylic resin veneering (Fig. 3). Both groups will receive titanium implants with sandblasted, large grid, and acid-etched surfaces. The trial will last for 5 years, and the patients will be followed up at 6-month intervals. During each visit, the patient will undergo a clinical examination, surface roughness test, and submucosa plaque collection, while biological and mechanical complications will be treated. One week before each visit, the patient will receive periodontal maintenance, including ultrasonic debridement using an ultrasonic device with polyetheretherketone-coated tips (AIRFLOW® Prophylaxis Master; EMS Dental, Nyon, Switzerland) combined with erythritol air-polishing (AIR-FLOW® handy 3.0 PERIO; EMS Dental). X-ray assessment will be performed yearly. A treatment timeline is shown in Table 1.

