### Interventions

The aim of the treatment protocol is to rehabilitate these patients with full-arch fixed implant-supported prosthesis with placement of 4–6 implants in the mandible. Patients will be randomly assigned to receive one of two restorative materials: zirconia ceramic frameworks with or without ceramic veneering vs. titanium frameworks with acrylic resin veneering. Before prosthesis fitting, the patients will undergo a standard polishing procedure (GB/T 6060.2-2006) and examination to ensure the same surface roughness between groups. The surface roughness of all specimens will be measured with the use of a profilometer (Mitutoyo Surftest SJ-401; Mitutoyo Corporation, Kawasaki, Japan), as described in a previous study [19]. The implant number, implant site, implant diameter, implant length, implant torque, distances between the inserted implants, and shapes of the intaglio surface will be recorded as basic information.

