### Randomization, allocation, and blinding

The subjects will be randomly allocated to one of two groups according to the prosthetic materials: titanium framework with acrylic resin veneering (group 1) or zirconia framework with/without ceramic veneering (group 2). The allocation of patients will be randomized using computer-generated permuted block randomization with an allocation ratio of 1:1. Randomization will be performed by sealed envelopes that will be opened after final impressions are obtained.

Microbiota analysis will be blinded after assignment to the intervention groups. Each sample will have a number associated with an allocation sequence, as well as information pertaining to the dental position and acquisition time. The technician conducting the PCR analysis will be blinded to the source of the sample. Interim statistical analysis will be performed at 1 and 3 years after implantation of the final prostheses. Final statistical analysis will be conducted at the end of the trial with the analyst blinded to both patient allocation and the interim analysis results.

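### The trial compares two prosthesis systems that differ in framework and veneer together, so it cannot support the zirconia-versus-titanium material inference in its Discussion

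*Protocol article*

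**What the plan says.** **Arms.** Study design and setting assigns "zirconia frameworks with ceramic veneering (Fig. 2) or titanium frameworks with acrylic resin veneering (Fig. 3". The Abstract (Methods) agrees: in the second group "the participants will receive titanium frameworks with acrylic resin veneering". The Objectives use the same pair to spell out what the two restorative materials are: "zirconia frameworks with ceramic veneering vs. titanium frameworks with acrylic resin veneering".

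**A second definition of the zirconia arm.** Interventions gives "zirconia ceramic frameworks with or without ceramic veneering vs. titanium frameworks with acrylic resin veneering", and Randomization, allocation, and blinding gives "zirconia framework with/without ceramic veneering (group 2". In these two sections the ceramic veneer is optional.

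**Inference.** The Abstract (Background) puts the aim as the effect of material properties on biofilm. The Abstract (Discussion) says the comparison serves "to determine whether zirconia is an appropriate material for fixed implant-supported prostheses for edentulous patients". The main Discussion places its hypothesis in corrosion and aging of the framework and says the work "will provide scientific evidence of the differences in the material properties of zirconia and titanium in terms of the influence on biofilm formation".

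**Control of surface differences.** Prostheses are polished to the same roughness before fitting. The Discussion then says that charge, energy, topography and stiffness of the surface also affect how bacteria respond. It notes that the two framework-veneer combinations differ mechanically and takes this up for wear, fracture and chipping, and for the roughness change that chipping may cause. It does not present the veneer material itself as another explanation for a microbial difference.

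**The concern.** A between-arm difference in plaque, bleeding, bone loss or microbiota could come from the framework, from acrylic versus ceramic, or from both. Effects in opposite directions could also cancel and be read as no difference between materials. A reader who follows the Discussion would then credit or blame zirconia or titanium for something the randomisation cannot assign to either.

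The article also sets itself a standard here. Its Background criticises earlier studies for uncontrolled interfering factors and offers full-arch restorations of equal smoothness as the remedy. A second material that changes with the arm is an interfering factor that equal smoothness at delivery does not remove.

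**Working it through.** No stated figure bears on the point, so the check is of what the design identifies.

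**1. Layout of the arms** (Abstract Methods, Objectives, Study design and setting):

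| | Ceramic veneer | Acrylic resin veneer |
|---|---|---|
| Zirconia framework | arm present | none |
| Titanium framework | none | arm present |

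Two of the four cells are filled.

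**2. What the arm difference estimates.** Let F be the framework effect (zirconia minus titanium) and V the veneer effect (ceramic minus acrylic), ignoring interaction. The expected arm difference is D = F + V. That is one equation in two unknowns. The indicators for arm, titanium framework and acrylic veneer are the same variable (correlation 1).

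**3. Illustration with the article's own planning figures.** The Sample size section takes 0.6 mm bone loss for ceramic and 0.9 mm for metal-based prostheses, so D = 0.6 − 0.9 = −0.3 mm. All of these fit equally well:

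- F = −0.3, V = 0: all framework
- F = 0, V = −0.3: all veneer
- F = −0.15, V = −0.15: half each
- F = +0.3, V = −0.6: framework effect of opposite sign

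These splits are illustrations, not estimates. A larger sample makes D more precise and leaves the split as open as before. The 0.9 mm planning figure itself pools metal-resin with metal-ceramic prostheses, so it does not isolate a veneer either.

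**4. Can adjustment separate them?** Statistical analysis names the shape of the intaglio surface, the distances between implants and other confounders. Veneer is not named, and if it were added it would be collinear with arm.

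**5. Does an optional ceramic veneer help?** Suppose a proportion p of zirconia prostheses is veneered. Let V be the effect of ceramic versus acrylic and W the effect of no veneer versus acrylic. Then D = F + pV + (1 − p)W. Veneering now varies, but only within the zirconia arm and not by randomisation, while every titanium prosthesis still has acrylic resin. F remains unidentified.

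**6. Inference against design.** The comparison in the Objectives is D, and the trial estimates it. The claim about zirconia and titanium properties, and the hypothesis about framework aging, concern F, which the trial does not estimate.

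**The case against.** The strongest reply is that the trial already asks the right question. The Objectives define the materials as complete systems, the Background ends with an aim about titanium-based and zirconia-based prostheses, and the title names prostheses. The design is called pragmatic, and the closing line of the Discussion is about choosing a prosthesis. All of this stands. A reader might infer that the trial fails its own objective, but the documents do not support that: the system comparison is valid and useful.

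A second reply is that the veneer may lie away from the sampled zone. The Discussion speaks of polished framework surfaces, roughness is measured around each abutment, and plaque is taken from the base of the sulcus after supramucosal plaque is removed. This could make the veneer's influence on the microbiota small. However, the text does not say which material faces the mucosa, and the figures are not available here. The possibility limits what can be said about size; it does not separate the two effects.

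A reader might also fault the article for not listing the mucosa-facing material among the items recorded at delivery, where "distances between the inserted implants, and shapes of the intaglio surface will be recorded as basic information". That is form-level detail which an article may leave to the full protocol. Recording it would give only a non-randomised description and would not break the aliasing.

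Finally, the combinations are openly named and their mechanical difference is disclosed. What is missing is the extension of that limitation to the biofilm and microbiota inference.

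**Conclusion.** The point holds for the material-level inference only. The trial can answer its system-level objective. It cannot attribute a difference, or the absence of one, to zirconia versus titanium, nor test the framework-specific hypothesis.

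No magnitude can be given. A reader might take the splits above, from none to all of the difference or a reversed sign, as a measure of bias. They show only that the framework share is not identified. The conclusion rests on the arms as described, with no titanium prosthesis veneered in ceramic and no zirconia prosthesis veneered in acrylic. It holds whether the ceramic veneer is always present or optional.

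Arms, outcomes, tests and sample size need not change on this account. What changes is what the trial may conclude.

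**What to change.** 1. Reword the aim in the Abstract (Background) and the aim and planned conclusion in the Discussion as a comparison of two prosthesis systems, matching the Objectives. Present framework corrosion and aging as a possible explanation that the trial does not test.
2. Add the veneer difference to the stated limitations for the biofilm and microbiota results, not only for mechanical complications.
3. Reconcile the definition of the zirconia arm: veneered in the Abstract, Objectives and Study design and setting; optionally veneered in Interventions and in Randomization, allocation, and blinding. The system being compared must be described in one way throughout.
4. Optionally, record the material facing the mucosa at each sampled implant and report outcomes by it, labelled as descriptive.

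Items 1 to 3 are text changes, and item 4 is one extra field. The price is a narrower claim. Separating framework from veneer would need a common veneer in both arms or a framework-by-veneer factorial, which is a different trial.
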